### Recruitment

Patients will be recruited from several centers: South London and Maudsley NHS Foundation Trust (catchment area: two million); North East London Foundation Trust Eating Disorders Service (catchment area 650,000); Barnet, Enfield & Haringey Mental Health NHS Trust (catchment area five million); Oxford Health NHS Foundation Trust (catchment area 1.1 million for Oxfordshire and Buckinghamshire).

### Data management

Data will be checked for entry errors by performing double data entry for 10% of the data. Quality of the data will be tested by examining the data for impossible values by looking at data ranges. No post treatment data will be released until the database is locked. Statistical analysis will be blind to treatment arm.

### Statistical analysis

Outcomes will be analyzed on an intention-to-treat (ITT) basis, that is, participants will be analyzed in the group to which they were randomized irrespective of their compliance with the assigned scheme.

#### Primary outcome analysis

BMI at pretreatment (baseline), posttreatment (six months) and follow-up (twelve months) will be analyzed using a linear mixed effects model. In this model, the explanatory variables with fixed effects are treatment (MANTRA or SSCM), time (six months or twelve months), the treatment x time interaction, baseline BMI and randomization stratifiers (severity of weight loss, AN-subtype, and previous hospitalization). Correlation due to seeing the same therapist will be modeled by random effects that vary at the level of the therapist (accounting for general therapist effects) and a second set of random effects that vary at the level of the therapist within a specific treatment (a therapist x treatment interaction accounting for therapy-specific therapist effects). Correlation due to repeated measures will be accounted for by subject-varying random effects. Models will be fitted using maximum likelihood [49]. Model fitting will produce treatment effects estimates at posttreatment (secondary BMI outcome) and twelve months (primary BMI outcome). In the case of missing values in posttreatment BMI, the analysis is valid under the missing at random (MAR) assumption which stipulates that missingness is only driven by variables included in the mixed model. We will summarize the relation between demographic and clinical variables at baseline and study drop-out by twelve months (that is, those lost to follow-up or who actively withdrew from the study). Any baseline variables found to be predictive of missingness will be included as further explanatory variables in the mixed model.

Adherence with allocated treatment will be measured by the number of sessions attended and patients classified as ‘MANTRA completers’, ‘SSCM completers’ or ‘non-completers. Treatment completion will be defined as attending a minimum of 15 out of 20 weekly sessions [50]. In the case of non-adherence with randomized treatments, the ITT estimate no longer provides an efficacy assessment (only effectiveness under the current setting) and we will estimate the outcome difference between those receiving SSCM and MANTRA (relative efficacy, or more specifically the complier average causal effects or CACE) using instrumental variables methods (see for example, Dunn *et al*. [51]).

#### Secondary outcome analyses

Secondary outcome variables are all continuous and will be analyzed in the same way as the BMI variables. There are a considerable number of assessments of treatment effects on secondary outcomes. Thus interpretation of these treatment effect estimates will need to take into account the impact of multiple inferences.

##### Exploratory mediation assessment

Four of the secondary outcomes were chosen since they measure the core maintenance factors targeted by the MANTRA intervention. In other words these variables are putative mediators of the effect of MANTRA on patient ED outcomes. We will use the Baron and Kenny regression approach [52] to assess the potential of each of these four variables as mediators of patient ED outcomes (BMI and EDE global score). Such analyses make restrictive assumptions; the most important being that there is no hidden confounding of the effect of the mediator on the outcome. Thus we only use this as an exploratory approach to empirically re-formulate our basic (theoretical) MANTRA process model. The parameters of this model will yet have to be estimated without bias from future studies that have been designed for mediation analysis.

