### Aims

The main aim of this study is to compare the efficacy, cost and cost-effectiveness of MANTRA in adult outpatients with AN with that of SSCM in an RCT in a new larger sample.

The subsidiary aim of the study is to explore mediators and moderators of treatment outcome.

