### Research plan

#### Trial design

This is a multi-center two-arm superiority trial which will evaluate the efficacy and cost-effectiveness of MANTRA compared to SSCM, in consecutive referrals of adult outpatients with AN. Patients will be randomly allocated to either MANTRA or SSCM. More detail regarding the randomization procedure is provided below. Patients in both groups will be offered the same amount of therapy.

The study design is shown in Figure 1.

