### Outcome measures

All outcome measures will be collected at baseline, six and twelve months, except the treatment credibility/acceptability visual analogue scale (VAS) which will be collected only at six and twelve months. Potential mediators of treatment outcome will also be collected at three months (midtreatment).

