### Sample size

We observed a mean weight gain of 7.3 kg (standard deviation 4 kg) in an unpublished series of nine pilot patients treated with MANTRA. The mean weight gain for SSCM was previously estimated as 4 kg (McIntosh *et al*. [18]). We derived a conservative estimate of the group difference by a low estimate of the weight gain under MANTRA (mean – 0.8 × standard error = 6.5 kg) minus the weight gain estimate for SSCM; giving a difference of 2.5 kg. A sample size of n = 55 per group will have 90% power to detect a difference in mean weight gain of 2.5 kg assuming a common weight gain standard deviation of 4 kg (as per unpublished series of the nine pilot patients) and using an independent samples *t*-test with a significance level of alpha = 0.05. Correcting for 20% attrition (as found in our previous studies), a total of 138 patients will be needed. (The sample size calculation was not inflated for therapist effects because therapists were crossed with treatments, which allows us to take account of general therapist effects in the analysis, and treatment-specific therapist effects were thought to be negligible).

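### The Baron and Kenny mediation analysis, in its classical form, can miss real mediation if the between-arm difference is smaller than planned, and gives no interval for the indirect effect (minor)

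*Protocol article*

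**What the plan says.** Under Aims, the protocol article states: "The subsidiary aim of the study is to explore mediators and moderators of treatment outcome". The section Exploratory mediation assessment then fixes the method: "We will use the Baron and Kenny regression approach". It is applied to each of four secondary outcomes regarded as putative "mediators of patient ED outcomes (BMI and EDE global score").

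The same section limits what rests on the result. It calls the assumptions restrictive, "the most important being that there is no hidden confounding of the effect of the mediator on the outcome", and continues: "Thus we only use this as an exploratory approach to empirically re-formulate our basic (theoretical) MANTRA process model". Unbiased estimation is left to later studies designed for mediation.

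The data for a time-ordered analysis exist. Under Outcome measures: "Potential mediators of treatment outcome will also be collected at three months (midtreatment"), in addition to baseline, six and twelve months.

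The section does not say whether a significant total effect is a precondition, or whether the indirect effect will be estimated with an interval.

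**The concern.** The classical form of the named method is a sequence of significance tests: arm on outcome, arm on mediator, then mediator on outcome given arm. Mediation is concluded only if all three are significant. Two consequences follow.

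- **The first test acts as a gate.** Its power is that of the total treatment effect, which can be much lower than the power to detect the two paths.
- **The output is a set of verdicts.** The sequence does not itself give a size or a confidence interval for the pathway through the mediator.

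The article's caveat concerns hidden confounding, which is a matter of bias. It does not address lost sensitivity. Because the results are meant to reshape the MANTRA process model, a true mediator could be dropped from it only because the total effect missed p < 0.05. If the total effect is not significant, whether MANTRA moved its targets, and whether those targets relate to outcome, would be among the more useful things left to learn.

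**Working it through.** **Inputs from Sample size:** difference 2.5 kg, common SD 4 kg, 55 per group, alpha 0.05 (taken as two-sided, which reproduces the stated figures), 90% power, 20% attrition.

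**Step 1: reproduce the plan's figure.** The normal approximation is n = 2(1.960 + 1.282)² × (4/2.5)² = 2 × 10.51 × 2.56 = 53.8 per group. The exact two-sample t-test gives 54.8, so 55, with power 0.901. For attrition, 110/0.8 = 137.5, so 138. The stated 55, 138 and 90% all reproduce.

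**Step 2: chance of passing a total-effect gate.** This is the t-test power at 55 per group with standardised difference d = difference/4.

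| True difference | d | Gate passed |
|---|---|---|
| 2.5 kg (planned) | 0.625 | 90% |
| 2.0 kg | 0.500 | 74% |
| 1.5 kg | 0.375 | 50% |
| 1.0 kg | 0.250 | 26% |
| 0.5 kg | 0.125 | 10% |

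The even-odds point is about 1.96 × 4 × √(2/55) = 1.495 kg, or 1.495/2.5 = 60% of the planned effect.

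**Step 3: what the gate costs in mediation findings.** Two simulations were run with 55 per group. In both, the gated rule needs p < 0.05 for the total effect and for both paths. The ungated rule needs p < 0.05 for the two paths only. The path sizes are assumptions; the article gives none.

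*(a) Total effect set directly.* The standardised arm effect on the mediator is 0.5 or 0.8, and half or all of the effect is mediated. At 2.5 kg full mediation with an arm effect of 0.5 is infeasible, so that cell is absent.

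| True difference | Gated | Ungated |
|---|---|---|
| 2.5 kg | 71–90% | 74–98% |
| 1.5 kg | 34–48% | 68–99% |
| 1.0 kg | 9–24% | 36–90% |

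At the planned effect the gate loses 3% to 9% of the ungated detections. At 1.0 kg it loses 68% to 76% of them.

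*(b) Paths set directly.* Here there is full mediation and unit residual variances. With arm-to-mediator path a and mediator-to-outcome path b, the implied standardised total effect is d = ab/√(1 + b²), and 4d gives kilograms.

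| a, b | d | Implied kg | Gated | Ungated |
|---|---|---|---|---|
| 0.5, 0.4 | 0.20/1.077 = 0.19 | 0.74 | 14% | 74% |
| 0.6, 0.5 | 0.30/1.118 = 0.27 | 1.07 | 28% | 87% |
| 0.8, 0.5 | 0.40/1.118 = 0.36 | 1.43 | 46% | 98% |

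The t-test power at these values of d is 16%, 29% and 46%, so the gated rate is almost entirely the power of the first test. A percentile bootstrap interval for ab detects about as often as the ungated rule (75%, 89% and 98%). With no arm effect on the mediator its false-positive rate is about 5%.

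**Step 4: is a smaller difference plausible on the article's own figures?** The MANTRA gain of 7.3 kg comes from nine pilot patients with SD 4 kg, so its standard error is 4/√9 = 1.33 kg. The 95% t-interval is 7.3 ± 2.306 × 1.33, or 4.2 to 10.4 kg. Set against 4 kg for SSCM, taken as fixed, the lower limit implies a difference of about 0.2 kg. A difference of 1.5 kg needs a MANTRA gain of 5.5 kg, which is (7.3 − 5.5)/1.33 = 1.35 standard errors below the pilot mean. A true difference below 1.5 kg therefore cannot be ruled out, though the article does not predict one.

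**The case against.** **The gate is not written down.** The article names a regression approach and gives no stopping rule. The three regressions can be fitted, and the indirect effect reported, whatever the total effect. Step order and interval method are details that a condensed article may leave to the analysis plan. This stands, and it makes the point conditional. What remains is that the article names a method whose classical form carries the gate and does not set that form aside.

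**A reader might infer that, with two active treatments, real mediation will usually be missed.** The documents do not support this. Trial design says "This is a multi-center two-arm superiority trial", and Sample size says "A sample size of n = 55 per group will have 90% power to detect a difference in mean weight gain of 2.5 kg". The 2.5 kg is already the difference from the active comparator, so an active comparator does not by itself imply a low pass rate. At that difference even a strict gate passes about 90% of the time. Missing more often than not because of the gate requires a true difference below about 1.5 kg, which no section gives. The scenarios in Step 3(b) all imply at most 1.43/2.5 = 57% of the planned effect. They show the mechanism and do not forecast this trial.

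**A reader might also infer that the size of each pathway will go unreported.** That would rest on silence alone. The classical sequence does not supply an indirect effect with an interval, but the article does not rule one out.

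**The analysis is exploratory.** No efficacy conclusion depends on it, and the proposed replacement needs the same no-hidden-confounding assumption. Both statements are correct and lower the severity. Neither addresses lost sensitivity, which matters in work meant to generate hypotheses.

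**Conclusion.** The point holds in conditional form and is minor. If the classical form is applied, the total-effect requirement costs little at the planned 2.5 kg. It passes about half the time at 1.5 kg and about a quarter of the time at 1.0 kg, and mediation is then missed although both paths are detectable.

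The size rests on assumptions:
- The pass rates use an unadjusted t-test on weight gain in kilograms. The mediation outcomes are BMI and EDE global. The planned baseline-adjusted mixed model could have higher power than these figures.
- No effect size, SD or power is stated for EDE global, so the 90% pass rate cannot be carried over to it.
- The detection rates depend on assumed path sizes and on no mediator–outcome confounding.

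**What to change.** In Exploratory mediation assessment, replace the named approach with direct estimation of the indirect effect:

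1. Regress the three-month mediator on arm, baseline mediator, baseline outcome and the randomization stratifiers.
2. Regress twelve-month BMI, and separately EDE global, on arm, the three-month mediator and the same baseline variables.
3. Report the product of the arm-to-mediator and mediator-to-outcome coefficients with a bootstrap 95% interval for every mediator and outcome, whether or not the total effect is significant.

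Keep the exploratory label and the caveat on hidden confounding, which applies equally to this method. The cost is a change of wording and a few lines of code. The baseline, three-month and twelve-month measurements are already scheduled.

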##### Exploratory moderation assessment

The study was not powered to detect treatment effect modification by baseline variables. We will carry out exploratory moderator analyses by including interactions between treatment and putative moderators (see potential moderators’ list above) in respective linear mixed models. The results will suggest moderation hypotheses to be investigated in future trials.

All analyses will be carried out in Stata 12 [53].

#### Economic analysis

Service use patterns will be described and service costs calculated using a well-established compendium of unit costs [54] or those specifically estimated for this study, using a comparable estimation method. Use of MANTRA and SSCM will be recorded by therapists on the case record form noting the number of sessions each participant attended, the duration of each session and details of staff involved in providing the intervention. From these data, the cost of the intervention will be estimated.

Cost-effectiveness analysis will then be conducted for the period from baseline to twelve months follow-up using the primary outcome measures, and the CIA.

### Reporting of trial

The trial data will be reported in line with the extension of CONSORT guidance for trials assessing non-pharmacological treatments [55,56].

## Discussion

The aim of the MOSAIC study is to compare the efficacy, cost and cost-effectiveness of two manual-based treatments, MANTRA and SSCM, in adult outpatients with AN and EDNOS-AN. The secondary aim is to explore mediators and potential moderators of treatment outcome.

Psychotherapeutic interventions are the treatment of choice for AN and related conditions. However, the evidence-base for such treatments of adults with AN is extremely limited. A number of small trials have tested a range of therapies, yet there is no clear front runner. There is an urgent need to develop more efficacious treatments for adults with AN. Previous psychosocial treatments for AN have been adapted from those for other disorders and the effectiveness of a tailor-made intervention is yet to be tested. MANTRA is a treatment based on a specific maintenance model of AN. It draws on neuropsychological, social-cognitive and personality trait research in AN and includes both intra- and interpersonal maintaining factors. It also has some preliminary evidence for acceptability and effectiveness among the AN patient group [19,20].

The comparison treatment, SSCM, has been selected as it was found to be superior to two other active treatments [18] and is therefore a suitable alternative to MANTRA. However, the advantages of SSCM appear to fade over time [50]. Therefore longer-term follow-up is needed to determine whether treatment effects of SSCM and MANTRA persist over time, which we plan to explore in future studies.

### Potential implications

The MOSAIC study is the first large-scale RCT to compare the efficacy of MANTRA and SSCM for adult outpatients with AN or EDNOS-AN. The economic analysis will give insight into the total cost of treating the disorder and inform future best practice guidance. The results of this study will provide a rigorous evaluation of a novel treatment for AN (MANTRA) which could be implemented in the NHS and made available to services across the UK.

### Strengths

This trial has a number of strengths. In particular the large sample size provides sufficient power to draw meaningful conclusions. Generalizability of results is facilitated by maximizing recruitment; four separate sites participate in the study and the broad inclusion criteria ensure inclusion of patients along the full spectrum of AN severity. Therapist bias is reduced as all therapists treat patients using both MANTRA and SSCM, and research bias is reduced by researcher blinding to treatment and stratified randomization. To help prevent trial drop-out, treatment and research are kept separate.

### Challenges

Maintaining motivation over the prolonged study period may be challenging. All clinical and research personnel involved in MOSAIC will receive a monthly newsletter providing updates on recruitment, answering queries, and offering encouragement to each NHS site. There will also be a facility to allow anonymous feedback from clinicians about their experience of the two interventions and of taking part in an RCT. Quality control measures have also been considered. To avoid therapeutic drift, clinicians will receive ‘booster’ training days over the course of the study and work using separate treatment manuals. Therapists will attend weekly supervision by senior clinicians. Supervision for MANTRA and SSCM will be carried out separately to avoid contamination across therapies. Psychotherapeutic sessions will be audio taped and case record forms will be kept for individual patients to ensure adherence to treatment protocol and the uniformity of treatment delivery. To aid in participant retention we will keep a certain level of continuity in the researcher-participant pairing and collect alternative contact information should participant circumstances change. Through understanding that research assessments may seem arduous at times, we aim to accommodate participants wherever possible by offering home visits, telephone interviewing and financial reimbursement.

## Conclusion

To conclude, this paper sets out a protocol for a multi-center RCT that will enhance the current knowledge of the relative efficacy of potential treatments for AN, using a number of neuropsychological, social cognitive and psychological measures.

## Trial status

Recruitment for the trial is on-going. Data collection will continue until end of 2013.

## Abbreviations

AN: Anorexia nervosa; BMI: Body mass index; CACE: Complier average causal effects; CBT: Cognitive behavioral therapy; CIA: Clinical Impairment Assessment; CSRI: Client Services Receipt Interview; CTU: Clinical trials unit; DASS-21: Depression Anxiety, Stress Scale – 21; DSM-IV: Diagnostic and Statistical Manual of mental disorders; EDE: Eating disorder examination; EDEQ: Eating disorder examination questionnaire; EDNOS: Eating disorder not otherwise specified; EDNOS-AN: Eating disorder not otherwise specified anorexia nervosa type; IPT: Interpersonal psychotherapy; MANTRA: Maudsley Model of Treatment for Adults with Anorexia Nervosa; MAR: Missing at random; MHRN: Mental Health Research Network; MISC: Motivational Interviewing Skills Code; MITI: Motivational Interviewing Treatment Integrity; MOSAIC: Maudsley Outpatient Study of Treatments for Anorexia Nervosa and Related Conditions; NART: National Adult Reading Test; NICE: National Institute for Health and Clinical Excellence; NIH: National Institute of Health; OCI: Obsessive compulsive inventory; RCT: Randomized controlled trial; SSCM: Specialist supportive clinical management; VAS: Visual analogue scale; WHO: World Health Organization
